### **4.7.2 Sample size**

Considering the lack of previous studies combining music-guided walking with singing, we calculated a sample size based on studies applying similar rehabilitation interventions(25, 26). The primary outcome is the distance of ISWT and the sample size was based on change in our primary outcome from baseline to week 12. As suggested by similar studies, we assumed mean changes of multi-model MT group, rhythm-guided walking group and usual care group are 40 m, 27 m, and -15m, respectively(25, 26), and the combined standard deviations (SD) are 35 m, 38 m, and 40 m, respectively. A sample size of 9 patients per group yields a power of 90% at a 2-sided significance level of 5% with an ANOVA. Adjusting for approximately 50% dropout results in a target group size of 18 participants per study group and a total case number of 54.

[figure not shown]

Therefore, 75 participants are anticipated to be enrolled into this study.

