**4.3 Randomization, allocation concealment, and blinding**

All patients will be randomized in a 1:1:1 ratio (adhering to block randomization within each center) into three groups: Multi-module MT, rhythm-guided walking, and usual care groups using a table of random numbers generated in the SPSS statistical package held by an independent statistical analyst. Group information will be stored in an opaque envelope and sealed thereafter. After obtaining informed consent and baseline assessment, the study coordinator will unseal the envelope to obtain the random numbers and grouping information for each participant.

Due to the nature of the intervention, neither the participants nor the exercise instructors will be blinded. However, pulmonology and rehabilitation nurses conducting outcome assessments and statistical analysts will be blinded to the assignments.

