**4.7 Statistical analysis methods and sample size calculation**

### **4.7.1 Statistical analysis methods**

The primary analysis will be conducted as intention-to-treat (ITT), including all patients that received randomization. Continuous baseline characteristics are given as median (range) or mean (SD) as appropriate and categorical variables as frequencies. Three comparisons will be carried out: multi-module MT versus usual care, multi-module MT versus rhythm-guided walking and rhythm-guided walking versus usual care. All analyses will be carried out using two-sided significance tests at the 0.05 significance level. Our primary analysis will compare the treatment groups at 12 weeks. The primary outcome, ISWT distance, will be analyzed using a linear mixed model, including assessments at all available time points with reference to the date of randomization. The model will include treatment group, time point of measurement as fixed effects. Other covariates treated as fixed effects were the treatment by time point interaction, age (in years), gender (male or female), BMI and ISWT at baseline. The model included recruitment site as a random effect. The model will provide treatment group differences over 12 weeks as well as estimates at individual time points. These will be presented as mean estimates with 95% confidence intervals and associated p values. For the modelling of repeated measurements, the best fitting (based on AIC and BIC information criteria), simple (not significantly different from an unstructured pattern) covariance pattern will be selected. Model assumptions will be checked and, if they are in doubt, the data will be transformed prior to analysis or alternative non-parametric analysis methods will be used. The following outcomes will be analyzed analogously to the evaluation described above for the primary outcome : mMRC scores, quality of life measures, and anxiety/depression rate, MIP/MEP and pulmonary function parameters.

Two separate sensitivity analyses will be undertaken: multiple imputation for missing data, inclusion of participants receiving the randomly assigned treatment and completing the study (i.e., a per-protocol population).

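### The protocol's own means and SDs give about 78% ANOVA power at 9 patients per group, not 90%; 90% needs 12 evaluable patients per group

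*Protocol*

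**What the plan says.** Section 4.7.2 (Sample size) of the protocol sizes the trial on the primary outcome, ISWT distance: "the sample size was based on change in our primary outcome from baseline to week 12". The assumed effects are: "we assumed mean changes of multi-model MT group, rhythm-guided walking group and usual care group are 40 m, 27 m, and -15m, respectively". The assumed variability is: "the combined standard deviations (SD) are 35 m, 38 m, and 40 m, respectively". From these the section concludes: "A sample size of 9 patients per group yields a power of 90% at a 2-sided significance level of 5% with an ANOVA". It then inflates for losses: "Adjusting for approximately 50% dropout results in a target group size of 18 participants per study group and a total case number of 54". After a figure that is not reproduced in the text available here, it ends: "Therefore, 75 participants are anticipated to be enrolled into this study".

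Two other sections fix the remaining inputs. Section 4.3 gives equal allocation ("All patients will be randomized in a 1:1:1 ratio"), and section 4.7.1 confirms the significance level ("All analyses will be carried out using two-sided significance tests at the 0.05 significance level").

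**The concern.** The section prints every input to a one-way ANOVA power calculation: three means, three SDs, the group size, the significance level and the test. The power can therefore be checked without any outside assumption, and 90% from only 27 evaluable patients looks high for these means and SDs.

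The figure of 9 per group is the base of the sample-size argument, since 18 per group and 54 in total are that number doubled for dropout. If it is wrong, an ethics committee, funder or reader is told that 54 randomised patients, or 9 evaluable per group, suffice for 90% power when they do not. The sponsor could also treat 9 completers per group as enough.

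**Working it through.** **Inputs** (section 4.7.2 unless noted): mean changes 40, 27 and -15 m; SDs 35, 38 and 40 m; two-sided alpha 0.05; equal groups (section 4.3); one-way ANOVA on change from baseline to week 12.

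**Effect size**
- Grand mean = (40 + 27 - 15)/3 = 17.33 m.
- Sum of squared deviations = 22.67² + 9.67² + 32.33² = 1652.67.
- SD of the means = √(1652.67/3) = 23.47 m.
- Pooled variance = (35² + 38² + 40²)/3 = 4269/3 = 1423, so pooled SD = 37.72 m.
- Cohen's f = 23.47/37.72 = 0.622.

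**Attempt to reproduce the stated 90% at n = 9**
- Noncentrality λ = n × 1652.67/1423 = 9 × 1.1614 = 10.45.
- Degrees of freedom 2 and 24; critical F = 3.40.
- Power = P(noncentral F > 3.40) = **78.0%**.
- Simulation with the three unequal SDs gives 77.6% for the classical F test and 73.2% for Welch's version.

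The stated figure is not reproduced.

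**Other readings of the SD or the method, n = 9**

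| Variant | Power |
|---|---|
| SD 35 m in every group | 84.2% |
| SD 38 m in every group | 77.4% |
| SD 40 m in every group | 72.8% |
| Pooled SD, large-sample chi-square approximation | 83.3% |
| Pooled SD, alpha 0.10 | 87.1% |

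For 90% at n = 9 the common SD would have to be about 32.15 m, below each of the three stated SDs.

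**Calculations that do reach 90% at n = 9, but are not what the text describes**
- Dividing the sum of squares of the three means by 2 where the formula needs 3 inflates λ by 1.5. That gives 92.4% at n = 9 and 88.4% at n = 8, so 9 would be the first group size above 90%. This may be how 9 arose, but that is conjecture.
- A one-sided t test of multi-module MT against usual care alone gives 90.7%. The text states a two-sided ANOVA.

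**Group size that gives 90%** (pooled SD)

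| n per group | Power |
|---|---|
| 9 | 78.0% |
| 10 | 83.0% |
| 11 | 87.0% |
| 12 | 90.1% |
| 13 | 92.6% |

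Simulation with the unequal SDs gives 89.7% at n = 12.

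**Dropout**
- 12/(1 - 0.5) = 24 per group; 3 × 24 = 72.
- Planned enrolment: 75/3 = 25 per group; 25 × 0.5 = 12.5 evaluable, power about 91%.
- The stated 54: 18 × 0.5 = 9 evaluable per group, power 78.0%, so the chance of missing the assumed effect is 100% - 78% = 22%.

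**The case against.** The strongest reply is that the trial as planned is not short of patients. Enrolment is 75, and at the protocol's own 50% dropout that leaves about 12 to 13 evaluable per group and roughly 90 to 92% power for the overall F test. To fall to 9 per group from 25, dropout would have to reach 16/25 = 64%. This stands: it limits the practical harm. It does not make the sentence about 9 per group true, nor the 18 and 54 that follow from it.

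A second reply is that section 4.7.1 specifies a linear mixed model with baseline ISWT as a covariate, which could be more efficient than an ANOVA on change scores. That is possible. To give 90% at n = 9, residual variance would have to fall by about 27% (32.15²/37.72² = 0.73). The protocol gives no correlation to support this, and section 4.7.2 claims the power for an ANOVA. What stands is that the 22% applies to the ANOVA as stated and cannot be carried straight over to the mixed model.

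Third, 12 per group reaches 90% only narrowly. With the SDs kept unequal, simulation gives 89.7%, which still rounds to 90%. A sponsor insisting on strictly 90% or more on that basis would need 13 per group (92.2% simulated), hence 26 randomised per group and 78 in total, slightly above 75.

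Fourth, the figure that is not shown may explain how 75 was reached. The derivation of 75 is therefore not criticised here. The figure cannot reconcile the printed power with the printed means and SDs.

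**Conclusion.** The concern holds. Under the protocol's own assumptions, 9 patients per group give about 78% power for the two-sided 5% ANOVA, 12 percentage points below the stated 90%. The type II error is about 22%, more than double the stated 10%. The first group size to reach 90% is 12 evaluable, or 36 in all.

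This rests only on the printed means and SDs, equal groups and a pooled variance. Keeping the SDs unequal moves the result by less than one percentage point, and using any single stated SD throughout keeps power at n = 9 between 72.8% and 84.2%. The planned enrolment of 75 is large enough to offset the error at 50% dropout, so the power statement and the totals derived from it need correcting, but the recruitment target does not.

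The result concerns the overall F test, the only test for which the section claims power. It says nothing about the three pairwise comparisons in section 4.7.1.

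**What to change.** In section 4.7.2, replace 9 patients per group with 12 evaluable patients per group (power about 90%, two-sided 5%, one-way ANOVA, pooled SD 37.72 m). Replace 18 per group and 54 in total with 24 per group and 72 in total after 50% dropout, and note that the planned 75 covers this. The sponsor should confirm how 75 was reached and make the text agree with it. If 9 per group is to stay, its power should be restated as 78%.

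The cost is the wording of one paragraph. No patients beyond the planned 75 are needed, and neither the design nor the analysis changes.

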Recent studies have highlighted that music-facilitated rehabilitation not only benefits the interrelated physical and psychological consequences of patients but also improves motivation and training adherence. Music therapy (MT) targeting COPD includes passive (listening tomusic during aerobic exercises) and active elements (singing) (10, 11). Using rhythms to control the walking speed could offer an easy, economical way to ensure the exercise intensity at home. It can also be regarded as distractive auditory stimulus therapy, helping with dyspnea and fatigue during exertion (12). Additionally, singing promotes adaptation to breath control and training related respiratory muscles with less cost and more interest (13). Therefore, integrating tele-PR and MT may help overcome the previously mentioned barriers. However, there is a lack of relevant home-based studies as most of the existing studies were conducted in the hospital or community. Moreover there is limited evidence on the integrated effects of singing and music-guided aerobic exercises, with most studies only applying one kind of intervention (14).

Therefore, to identify a helpful and easy-to-use rehabilitation mode, our study aimed to develop a home-based, music-facilitated rehabilitation program for patients with COPD, using music tempo-guided walking exercises and breathing exercises, such as singing. Based on a thorough literature review, this is the first study to combine the two forms of MT for home-based PR and apply objective recording and supervision of training implementation using wearable sensors (a sports wristwatch that monitors step counts and walking distance) for music-facilitated tele-PR. This study protocol describes the process to investigate the efficacy and safety of the developed MT-facilitated telerehabilitation program (including rhythm-guided walking and singing).

**3.2 Objectives:** The primary aim of this study is to explore the efficacy of this home-based, MT- facilitated rehabilitation program (including rhythm-guided walking and singing). The secondary aim is to explore whether addition of singing training results in improvements compared with rhythm-guided walking alone.

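### The only stated power (90% at 9 per group) is for a three-group ANOVA that is not among the planned tests and does not reproduce; no power is given for the three pairwise comparisons, and multi-module music therapy versus walking has about 13–23% at the planned enrolment.

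*Protocol*

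**What the plan says.** Section 4.7.2 bases the sample size on the change in ISWT distance from baseline to week 12. The assumed mean changes for the "multi-model MT group, rhythm-guided walking group and usual care group are 40 m, 27 m, and -15m, respectively", and "the combined standard deviations (SD) are 35 m, 38 m, and 40 m, respectively". It then states that 9 patients per group "yields a power of 90% at a 2-sided significance level of 5% with an ANOVA". Next comes "Adjusting for approximately 50% dropout results in a target group size of 18 participants per study group and a total case number of 54", and finally "Therefore, 75 participants are anticipated to be enrolled into this study".

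Section 4.7.1 sets out the analysis: "Three comparisons will be carried out: multi-module MT versus usual care, multi-module MT versus rhythm-guided walking and rhythm-guided walking versus usual care". All tests are two-sided at 0.05. The primary analysis compares groups at 12 weeks using a linear mixed model, and results are given as mean estimates with 95% confidence intervals and p values. Neither an ANOVA nor a global test across the three arms is named.

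Section 3.2 makes the efficacy of the full programme the primary aim. On singing it says: "The secondary aim is to explore whether addition of singing training results in improvements compared with rhythm-guided walking alone".

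**The concern.** An omnibus ANOVA asks whether any of the three means differ. The planned tests each ask about one pair. On the assumed means the pairs are 55 m apart (MT versus usual care), 42 m (walking versus usual care) and 13 m (MT versus walking), so their powers must differ widely. One omnibus figure cannot stand for any of them.

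The omnibus test is also nearly blind to singing, because the two gaps to usual care drive it.

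At stake is how the results can be read. The protocol gives no figure showing how likely each planned comparison is to detect the effect it assumes. For the singing question, the likeliest result is non-significant even if singing works exactly as assumed. That should be on record before the data are seen.

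**Working it through.** **Inputs (section 4.7.2).** Mean changes 40, 27 and −15 m; SDs 35, 38 and 40 m; two-sided alpha 0.05. Numbers per group:
- 9: the stated requirement, which is also 54 enrolled with 50% dropout
- 12: 75 enrolled is 25 per arm at 1:1:1, and 25 × 0.5 = 12.5, rounded down
- 18: 54 enrolled with no dropout
- 25: 75 enrolled with no dropout

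**Step 1: the protocol's own figure.** The grand mean is (40 + 27 − 15)/3 = 17.33. The sum of squared deviations is 22.67² + 9.67² + 32.33² = 1652.7. The average variance is (1225 + 1444 + 1600)/3 = 1423, so the SD is 37.72 m. The noncentrality is λ = n × 1652.7/1423.

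At n = 9, λ = 10.45. With 2 and 24 degrees of freedom the critical F is 3.40 and the power is 78%. Alternatives at n = 9:
- simulation with the unequal SDs: 77.5%
- one common SD: 73% (SD 40) to 84% (SD 35)
- chi-square approximation: 83%

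None of these reaches 90%. Power is 87% at 11 per group and 90% at 12. The dropout step is correct: 9/(1 − 0.5) = 18.

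**Step 2: how much the ANOVA depends on singing.** Set MT and walking both to their average, 33.5 m, so that singing adds nothing. Omnibus power falls only from 78% to 76% at 9 per group, and from 90% to 88% at 12.

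**Step 3: the planned pairs.** I used the noncentral t with 2n − 2 degrees of freedom and noncentrality difference/(SD × √(2/n)). The SD for a pair is the square root of the mean of its two variances:
- MT versus usual care: √((1225 + 1600)/2) = 37.58 m
- walking versus usual care: √((1444 + 1600)/2) = 39.01 m
- MT versus walking: √((1225 + 1444)/2) = 36.53 m

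At n = 12 the noncentralities are 55/15.34 = 3.59, 42/15.93 = 2.64 and 13/14.91 = 0.87.

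| Evaluable per group | MT vs usual care (55 m) | Walking vs usual care (42 m) | MT vs walking (13 m) |
|---|---|---|---|
| 9 | 83% | 57% | 11% |
| 12 | 93% | 71% | 13% |
| 18 | 99% | 88% | 18% |
| 25 | >99% | 96% | 23% |

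MT versus walking would need about 125 evaluable per group for 80% power.

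**Step 4: precision for MT versus walking.** The 95% half-width is t × 36.53 × √(2/n). At 12 per group it is 2.074 × 14.91 = 31 m. At 25 it is 2.011 × 10.33 = 21 m. The assumed effect is 13 m.

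**Step 5: what the mixed model could add.** The protocol gives no correlations. As an assumption, let the covariates and repeated measures correlate 0.3 to 0.7 with the 12-week change, so that the SD shrinks by √(1 − r²). MT versus walking then has 14–21% power at 12 per group and 25–41% at 25.

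**The case against.** Several points on the other side stand.

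- Sizing a trial on its primary aim is ordinary practice. MT versus usual care, which matches that aim, has about 93% power at 12 evaluable per group. The singing question is secondary, its wording is exploratory, and the protocol claims no power for it.
- Enrolment of 75 also covers the ANOVA as it should have been calculated: 12/(1 − 0.5) = 24 per group, or 72 in total.
- The 9-per-group row corresponds to 54 enrolled, not 75, so 13–23% is the relevant range for MT versus walking before any gain from the model.
- Confidence intervals are already planned for every comparison.

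Some stronger readings are tempting but not supported:

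- A reader might infer that the protocol promises 90% for each comparison. It does not; the figure is attached to the ANOVA alone.
- A reader might infer that a global test is ruled out. The three-level treatment factor could yield one. The accurate statement is that section 4.7.1 names none and lists three pairwise comparisons.
- A reader might infer that the investigators will report a null singing result as no benefit. Nothing in the protocol says so.

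Section 4.7.2 also contains a figure, between the 54 and the 75, that I could not see. It may show where the 9 came from. It would not change what the printed means and SDs yield.

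**Conclusion.** The point holds as a mismatch between the power statement and the planned tests, together with a power figure that is wrong on its own inputs: about 78% rather than 90% at 9 per group. It does not show that the trial fails its primary aim.

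At the evaluable number implied by 75 enrolled and 50% dropout, walking versus usual care has moderate power (71%). MT versus walking is not powered for the assumed 13 m, and stays far below 80% with no dropout and under the most favourable correlation tried (41%).

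These results take the protocol's means and SDs as given, use unadjusted two-sided 0.05 tests as section 4.7.1 states, and approximate the mixed-model contrasts by two-sample t-tests. The correlations in Step 5 are assumptions.

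**What to change.** In section 4.7.2, replace the ANOVA sentence with the power of MT versus usual care at week 12, at the evaluable number expected from 75 enrolled (about 93% at 12 per group). Print the other two powers beside it (71% for walking versus usual care, 13% for MT versus walking).

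In section 4.7.1, add that the exploratory MT versus walking comparison is not powered for the assumed 13 m. State that it will be interpreted by its estimate and 95% confidence interval, with an expected half-width of about 31 m at 12 per group and 21 m at 25, and that a non-significant p value will not be reported as no benefit of singing.

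Do not enlarge the trial. The change needs no new patients or data. Its cost is a less favourable stated power for two of the three comparisons.

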# **5 Procedures for obtaining informed consent**

The study will be conducted in accordance with the Declaration of Helsinki and the Ethical Guidelines for Medical Research Involving Human Subjects. The explanatory and consent documents approved by our Clinical Research Review Committee will be given to the patient, sufficient explanation will be given in writing and orally, and the patient's free and voluntary consent will be obtained in writing. When information on risks that may affect patient consent is obtained, or when changes are made to the implementation plan, etc. that may affect patient consent, the patient will be promptly informed. If there is a revision to the study and the patient must decide whether or not to participate in that study, etc., the patient's consent will be obtained again using the newly approved explanation and consent document (revised version) by the Clinical Research Review Committee of the hospital.

# **6 Handling of personal data and other information**

Persons involved in the research shall comply with the provisions of the "Ethical Guidelines for Medical Research Involving Human Subjects" as well as the "Personal Information Protection Law" and other relevant laws regarding the handling of personal information. Create data with each patient's number for the relevant medical information, and by deleting personal information create a table of correspondences between the anonymized data and the number by deleting the personal information. These data are recorded on external storage media. The anonymized data will be kept by the researcher and the corresponding table will be kept by the Principal Investigator (PI) in a locked storage room at the principal study site.

Correspondence tables will be kept by the Principal Investigator (PI) in a locked storage room at the appropriate study site. The computer on which the anonymized data and corresponding tables are stored is on a computer separate from the other computers.

# **7 Methods of disclosing information on research**

**7.1 Research registration**

This study was registered at ClinicalTrials.gov (registration number: NCT05832814).

**7.2 Publication of research results**

The results will be published in the form of a medical article. In addition, they may then also be published in the general media like the Internet.

**7.3 Attribution of results**

The results of this research shall belong to the Study director and Principal Investigators of this research, other research members and collaborators, etc., and National Center for Respiratory Medicine.

# **8 Definition and Management of Adverse Events**

**8.1 Definition of Adverse Events**

Adverse Event: An adverse event means any undesirable or unintended injury or illness or symptom thereof that occurs to a research subject, whether or not causally related to the research conducted.

Serious adverse events: Adverse events of concern in this study include pneumothorax, myalgia associated with respiratory muscle fatigue, and exacerbated dyspnea.

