9. Safety measurements: All adverse events (AEs) that occur during the study will be recorded and evaluated for relevance to the intervention. AEs include exacerbations, exercise injuries, and falls

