**8.2 Recording and Reporting of Adverse Events**

Clinical adverse events may arise during the examination of study participants. If an adverse event (including a serious adverse event) occurs, it must be thoroughly documented in the case report form, noting the time of occurrence, clinical manifestations, management steps, duration, and outcome of the event. For a serious adverse event, a serious adverse event form must be completed and immediately reported to the ethics committee.

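### The serious adverse event entry in section 8.1 lists three events of concern and gives no seriousness criterion, so what triggers immediate reporting under 8.2 is not fixed

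*Protocol*

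**What the plan says.** Protocol section 8.1 first defines an adverse event broadly, as "any undesirable or unintended injury or illness or symptom thereof that occurs to a research subject, whether or not causally related" to the research. The next entry, headed as serious adverse events, reads in full: "Serious adverse events: Adverse events of concern in this study include pneumothorax, myalgia associated with respiratory muscle fatigue, and exacerbated dyspnea". It sets no threshold of severity or outcome.

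Section 8.2 has two tiers. For any adverse event, serious or not, "it must be thoroughly documented in the case report form, noting the time of occurrence, clinical manifestations, management steps, duration, and outcome of the event". The second tier applies only to the serious category: "For a serious adverse event, a serious adverse event form must be completed and immediately reported to the ethics committee".

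Section 4.5, item 9, makes safety a secondary outcome. All adverse events are to be recorded and evaluated for relevance to the intervention, and "AEs include exacerbations, exercise injuries, and falls". It does not say when any of these becomes serious.

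**The concern.** The text under the SAE heading answers a different question from the one the heading asks. It says which events the investigators are watching for, not what makes an event serious. That would be only untidy if nothing depended on it, but section 8.2 uses the category as the trigger for expedited reporting.

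Two things are at stake.

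- **Participant protection.** The trial enrols patients with COPD of GOLD II-IV and has two arms exercising at home (4.2, 4.4). Patients are recruited from five hospitals, and without a criterion the staff handling an event must decide for themselves whether a death, an admission or a disabling injury calls for the SAE form.
- **Meaning of the safety data.** Section 3.1 names safety as something the study investigates. An SAE count collected under this entry would mix a potentially grave event (pneumothorax) with myalgia and dyspnea of any degree. It could not be read as a count of serious events.

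**Working it through.** No arithmetic applies, because the point concerns a definition. The check has three steps.

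**Step 1. Look for a seriousness criterion anywhere in the protocol.**

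- Role of Study Director (section 2): the director reports necessary information to the heads of institutions and the ethics committee so that adverse events can be assessed. No criterion and no timing.
- Table 1 (4.1): adverse events are collected at V1, V2 and V3. No grading.
- 4.5, item 9: three kinds of adverse event are named. None is graded.
- 8.1: a broad definition of an adverse event, then three named events under the SAE heading. No criterion.
- 8.2: refers to SAEs and sets the duty. No criterion.

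None of these places mentions death, threat to life, hospitalisation or disability.

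**Step 2. Apply the text as written to particular events.**

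| Event | Adverse event? | Position under the SAE entry in 8.1 | SAE form and immediate report under 8.2? |
| --- | --- | --- | --- |
| Pneumothorax | Yes | Named | Yes |
| Mild myalgia associated with respiratory muscle fatigue | Yes | Named, no severity threshold | Yes |
| Mild exacerbated dyspnea | Yes | Named, no severity threshold | Yes |
| Hospitalised exacerbation | Yes (also 4.5) | Not named; could be read as exacerbated dyspnea | Not fixed |
| Fall with serious injury | Yes (also 4.5) | Neither named nor excluded | Not fixed |
| Fatal event | Yes | Neither named nor excluded | Not fixed |

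The three rows with a definite answer include two in which the event may be minor. The three rows with no definite answer are those in which the outcome is grave.

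**Step 3. Ask whether 4.5 and 8.1 contradict each other.** They do not. Item 9 of 4.5 gives examples of adverse events, and 8.1 lists events under the serious heading. Exacerbations, injuries and falls need not appear on an SAE list, since many are not serious. What is missing is the rule that says when one of them is.

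**The case against.** The strongest replies are these.

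- **The list is open.** The entry says 'include'. A reader might infer that a death is not an SAE under this protocol. The text does not support that: it neither excludes a death nor contains a rule that makes it an SAE. A hospitalised exacerbation may also fall under exacerbated dyspnea. This objection stands, and it is why the point is that the status of these events is not fixed.
- **Unlisted events still have a route upward.** A reader might infer that they would go unescalated. That goes too far. Section 8.2 has every adverse event documented through to its outcome, 4.5 has all of them evaluated for relevance to the intervention, and the study director has a general duty to inform the ethics committee. That duty has no timing, however, so what remains unfixed is the trigger for immediate reporting.
- **No comparison is harmed.** A reader might infer that SAE rates would be biased against both exercise arms. The documents do not support this. Section 4.7.1 plans no comparison of SAEs by arm. Only the multi-module arm does respiratory muscle training, so the myalgia item gives little reason to expect inflation in the walking-only arm, and dyspnea can worsen under usual care too. What remains is an unquantified possibility that myalgia raises the SAE count in the multi-module arm.
- **The SAE form may carry the criteria.** It is not shown, so this cannot be checked. Even if it does, 8.1 would still place myalgia of any severity under the SAE label, and the protocol text and the form would need to agree.

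Leaving the matter to a statistical analysis plan would not answer the point. The definition governs what sites report during the trial, which belongs in the protocol.

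**Conclusion.** The point holds. Section 8.1 puts a list of events of concern where a definition of seriousness should stand, nothing else in the protocol supplies one, and 8.2 hangs the SAE form and immediate ethics reporting on that category. This is more than missing detail, because the entry as stated sorts events in a way unrelated to their seriousness.

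The size is qualitative. Two of the three named events enter the expedited category at any severity, and the category has no rule for death, hospitalisation or disabling injury. Randomisation, the primary outcome and its analysis are not touched.

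The conclusion assumes that no seriousness criterion sits in a document not at hand, such as the SAE form. It does not assume that sites would in practice fail to report a death.

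**What to change.** 1. In 8.1, define a serious adverse event by its outcome: death, a life-threatening event, new or prolonged hospitalisation, persistent or significant disability, or an otherwise medically important event.
2. Move pneumothorax, myalgia associated with respiratory muscle fatigue, and exacerbated dyspnea to a separate list of events of special interest. Record it alongside the exacerbations, exercise injuries and falls of 4.5, item 9.
3. State that any event on either list is an SAE only when it meets the criteria in 8.1.
4. Leave the reporting rule in 8.2 as it stands, so that it applies to the corrected category, and bring the SAE form into line.

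The cost is a few lines of protocol text, a revision of the form, and a small change, up or down, in the number of expedited reports. Sample size, visit schedule and efficacy analysis do not change.
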